### Follow-up

Patients will return after 6 months of follow-up to be evaluated by physicians and psychologists with no knowledge of the treatment allocation. Each patient’s mRS will be assessed by a physician, and psychologists will evaluate quality of life and cognitive performance using the SF-36 questionnaire and the MoCA test.

## Statistical analysis

The analysis of outcome measures will be on the intention-to-treat population, including those who died during the first 21 days. Results will be presented as an adjusted common odds ratio (OR) with a corresponding 95% confidence interval (CI), with values of the common OR of less than 1 indicating a treatment effect in favor of glibenclamide, with values of *p* < 0.05 considered statistically significant. Additionally, an analysis using logistic regression will be performed with the same covariates as specified above, adopting the conventional dichotomy of favorable mRS (0–2) versus unfavorable mRS (3–6). We will perform all analyses using the Mann Whitney *U* test, χ^2^ test or two-sample *t* tests as appropriate.

All statistical analysis will be performed with the SPSS Statistics for Windows software (IBM Corp., v. 24.0, Armonk, NY, USA). The analysis will also be blind for group allocations.

### Quality assurance

All data collected will be doubled checked by the study team and input into the REDCap system for storage and safe processing as a quality assurance measure.

### Expected outcomes

The primary outcomes will be the distribution of the mRS score assessed after 6 months of the end of the intervention, as favorable (mRS 0–2) and unfavorable (mRS 3–6). Secondary outcomes will be the cognitive assessment and quality of life as measured by the neuropsychological tests, as well as death, delayed ischemic deficits and the occurrence of serious adverse events attributable to medication. These secondary outcomes were preselected to provide supportive evidence related to the primary outcome.

The definition of delayed cerebral ischemia, as elaborated on by Vergouwen et al. [25], is taken as the occurrence of focal neurological impairment (such as hemiparesis, aphasia, apraxia, hemianopia, or neglect), or a decrease of at least 2 points on the Glasgow Coma Scale (either on the total score or on one of its individual components (eye, motor on either side, verbal)). This should last for at least 1 h, is not apparent immediately after aneurysm occlusion, and cannot be attributed to other causes by means of clinical assessment, computed tomography or magnetic resonance imaging of the brain, and appropriate laboratory studies. We will report any serious adverse events and those that were deemed to be related to the trial medication.

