**Methods:**

An estimated 80 patients meeting the inclusion criteria of radiological confirmatory evidence of an aneurysmal subarachnoid hemorrhage, age 18–70 years, and presentation of less than 96 h from the ictus will be allocated randomly into two groups, one receiving 5 mg daily oral intake of glibenclamide for 21 days and another control group receiving a placebo. The study’s primary outcome is the modified Rankin scale (mRS) after 6 months, as favorable (mRS 0–2) or unfavorable (mRS 3–6). The secondary outcomes will be late cognitive status, assessed after 6 months by psychological tests (the Short Form Health Survey Questionnaire and the Montreal Cognitive Assessment), as well as death at 6 months, delayed cerebral ischemia and occurrence of serious adverse events due to study medication.

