### Secondary objectives

The secondary objectives are to assess the safety and effect of glibenclamide on the mortality rate, quality of life and cognitive performance in patients with aneurysmal subarachnoid hemorrhage. A prospective, randomized, double-blind trial was designed to evaluate the following hypothesis: glibenclamide decreases mortality and improves quality of life and cognitive performance in patients with aneurysmal subarachnoid hemorrhage.

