### Safety considerations

An interim analysis will be performed when half of the sample size (40 patients) has completed the follow-up. An independent Data Monitoring Committee (DMC) will decide whether to stop or continue the trial after analyzing the evaluable data.

One of the investigators will have access to patient allocations to monitor possible side effects of glibenclamide, such as hypoglycemia. Capillary glycemia will be checked every 4 h during the 21-day treatment period and all measures to correct hypoglycemia will be taken. During the treatment time, no patients will be discharged.

The DMC will receive all data regarding the use of the drug and the possible side effects, as well the incidence of refractory hypoglycemia (serum glucose levels persistently < 70 mg/dL). If refractory hypoglycemia exceeds a frequency of 40% of treated patients, the trial will be interrupted. The same care will be taken for all other persistent events that are found.

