## Project duration and management

Patients will be evaluated by physicians at hospital admission, including intensive care physicians and neurosurgeons, to start complete management for subarachnoid hemorrhage. One of the researchers will apply the inclusion criteria and make the allocation with the randomly selected medication bottle. During the intervention, all adverse effects and neurological status will be recorded by the attending physicians. At the end of the follow-up period, physicians and the neuropsychologist will register the mRS and apply the neuropsychological tests. Once half of the sample is reached, one of the authors, previously selected by the safety committee, will have access to each patient’s allocation to determine the study’s continuity. At the end of the study, all data will be statistically analyzed for group comparisons.

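### The named adverse-event outcome counts only serious events attributed to medication, so the hypoglycemia measured every 4 h is compared between arms only under a generic statement

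*Protocol article*

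**What the plan says.** Under Secondary objectives, the protocol article puts safety first: "The secondary objectives are to assess the safety and effect of glibenclamide on the mortality rate, quality of life and cognitive performance".

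Safety considerations gives one investigator access to the allocations "to monitor possible side effects of glibenclamide, such as hypoglycemia". No other side effect is named. The monitoring is intensive: "Capillary glycemia will be checked every 4 h during the 21-day treatment period and all measures to correct hypoglycemia will be taken". No distinction by arm is made.

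The outcome lists are narrower. Expected outcomes gives cognition and quality of life, "as well as death, delayed ischemic deficits and the occurrence of serious adverse events attributable to medication". The abstract's Methods paragraph ends its list with "delayed cerebral ischemia and occurrence of serious adverse events due to study medication". Hypoglycemia is in neither list.

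Three other statements bear on the point:

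- Expected outcomes adds a reporting sentence: "We will report any serious adverse events and those that were deemed to be related to the trial medication".
- Safety considerations sends the DMC the side-effect data and the incidence of refractory hypoglycemia (serum glucose persistently below 70 mg/dL), with interruption of the trial above 40% of treated patients.
- Project duration and management says "During the intervention, all adverse effects and neurological status will be recorded by the attending physicians", and closes by stating that all data will be analyzed to compare the groups.

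**The concern.** The article names one expected harm, schedules an objective measurement of it, and then defines its adverse-event outcome through two judgments: was the event serious, and was it due to the medication? A low reading picked up at a scheduled check and promptly corrected need not be classed as serious. The better the monitoring works, the fewer episodes will reach the named outcome.

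What is at stake is the benefit-risk conclusion. The trial could report little or no difference in its named adverse-event outcome while measured hypoglycemia was clearly more frequent on glibenclamide in acutely brain-injured patients. Readings that do not depend on anyone's opinion would have no defined place in the results, and the headline safety result would rest on a judged count.

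**Working it through.** **1. Where a corrected low reading would be counted.** Take a value below 70 mg/dL found at a routine check, corrected, and not classed as serious.

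| Statement in the article | Does it capture the episode? |
|---|---|
| Secondary outcome list (abstract; Expected outcomes) | No: the event must be serious and attributed to medication |
| Reporting sentence (Expected outcomes) | Not as a serious event. If the word for the second group means related adverse events of any grade, yes, but only when someone judges the episode drug-related. If it means related serious events, no |
| DMC measure (Safety considerations) | No: persistent low values only, as a share of treated patients, to decide on interruption |
| Recording and general analysis statement (Project duration and management) | Yes in principle, if recorded as an adverse effect. No hypoglycemia variable, threshold, denominator or estimate is given |

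Only the last row supports a between-arm comparison regardless of seriousness and causality, and it does so in general terms.

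**2. How much information is scheduled.** Inputs: one check every 4 h; a 21-day treatment period; start allowed up to 96 h (4 days) after the bleed, with dosing to day 21 after the bleed; 80 patients randomised 1:1, so 40 per arm.

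- Checks per day: 24 / 4 = 6.
- Per patient: 6 × 21 = 126, or 6 × (21 − 4) = 6 × 17 = 102 with the latest start.
- Per arm: 126 × 40 = 5,040, or 102 × 40 = 4,080, before any loss through death or withdrawal.

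This shows the volume of data, not a bias.

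**3. Illustration of what the seriousness filter can do.** The article gives no hypoglycemia rates and no share classed as serious, so every rate here is an assumption. Suppose 25% of glibenclamide and 5% of placebo patients have at least one value below 70 mg/dL.

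- Expected patients: 0.25 × 40 = 10 and 0.05 × 40 = 2.
- SE of the difference: √(0.25 × 0.75/40 + 0.05 × 0.95/40) = 0.0766.
- Difference 0.20; 95% CI 0.20 ± 1.96 × 0.0766, that is 0.05 to 0.35.

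Now suppose that 10% to 50% of those patients have an episode classed as serious, and that all of these are attributed to the drug. The expected counts fall to 1–5 against 0.2–1. Power of the uncorrected chi-square test (two-sided 5%, 40 per arm), by exact enumeration of the two binomials:

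| Assumed rates | What is counted | Power |
|---|---|---|
| 35% vs 5% | any low value | 96% |
| 25% vs 5% | any low value | 76% |
| 12.5% vs 2.5% | serious only (50% share) | 44% |
| 2.5% vs 0.5% | serious only (10% share) | 1% |

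The direction is general: filtering by seriousness shrinks the counts and the power. The particular percentages follow from the assumed rates.

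**The case against.** The strongest reply is that nothing is lost. The attending physicians record all adverse effects with no seriousness filter, all collected data go into REDCap, and the article says all data will be compared between groups. Serious events are to be reported whether or not attributed, death is a listed outcome, and the DMC sees the side-effect data. In addition, a journal article leaves safety tabulation to the full protocol and analysis plan, which are not shown.

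Much of this stands, and it rules out several stronger readings:

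- A reader might infer that hypoglycemia would not be compared between arms at all. The general statement under Project duration and management contradicts that.
- A reader might infer that attributed serious events are the only safety outcome. Death is in the same list, and reporting extends to any serious event. The restriction applies to the adverse-event item.
- A reader might infer that the delayed cerebral ischemia definition hides harm, because it requires that the deficit "cannot be attributed to other causes by means of clinical assessment, computed tomography or magnetic resonance imaging of the brain, and appropriate laboratory studies". That exclusion is proper for defining ischemia, and neurological status and adverse effects are recorded separately.
- A reader might take the power figures as measuring a flaw in this trial. They rest on assumed rates and on treating the serious-event count as the only comparison.

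What does not stand is the argument that this is merely unshown detail. The article states its outcome list twice, and both versions fix a filter on seriousness and attribution. A general promise to compare all data does not define the measure for the one harm the article singles out, and it refers to physicians' records rather than to the scheduled readings.

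**Conclusion.** The point holds in limited form. Hypoglycemia is the only side effect named and systematically measured, but it is absent from the secondary outcomes, whose adverse-event item is limited to attributed serious events. The DMC measure covers refractory cases in treated patients only. A between-arm comparison is thus foreseen only generically, and the named adverse-event outcome can miss low values found and corrected at routine checks.

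The reading of the text needs no assumption beyond this: a corrected low value is not automatically a serious event. The size of any missed difference cannot be determined from the article. Under the assumed rates above, 10 against 2 affected patients would appear as 1–5 against 0.2–1. The primary outcome is not touched. This is a worthwhile and inexpensive improvement to the safety outcome, not a defect that invalidates the trial.

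**What to change.** Add to the secondary safety outcomes, under Expected outcomes and in the abstract, hypoglycemia from the scheduled readings, by randomised arm and regardless of seriousness or judged causality. Report:

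1. the number and percentage of patients with at least one value below the article's own 70 mg/dL, with the risk difference and 95% CI;
2. episodes per monitored patient-day, so that early death or early stopping does not lower the count by shortening observation.

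The article attaches 70 mg/dL to persistent serum values, whereas the scheduled checks are capillary, so the definition should state that it uses the capillary readings. Keep attributed serious adverse events as an additional outcome.

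The cost is wording, one extra table, and entry of the 4-hourly values into REDCap (or each patient's lowest value and episode count). The drug's safety profile may look less favorable. No extra visits or procedures are needed, and no change to monitoring, dosing or treatment is proposed.

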## Project duration and management

Patients will be evaluated by physicians at hospital admission, including intensive care physicians and neurosurgeons, to start complete management for subarachnoid hemorrhage. One of the researchers will apply the inclusion criteria and make the allocation with the randomly selected medication bottle. During the intervention, all adverse effects and neurological status will be recorded by the attending physicians. At the end of the follow-up period, physicians and the neuropsychologist will register the mRS and apply the neuropsychological tests. Once half of the sample is reached, one of the authors, previously selected by the safety committee, will have access to each patient’s allocation to determine the study’s continuity. At the end of the study, all data will be statistically analyzed for group comparisons.

## Discussion

This protocol evaluates the clinical effectiveness of glibenclamide in patients with acute brain aneurysmatic hemorrhage in a randomized, double-blind, placebo-controlled trial. Many other studies are already researching the effect of glibenclamide in brain edema and traumatic brain injury [17–23], but there is currently no study on aneurysmatic hemorrhage. More similar studies, like those of Jiang et al. [24] and Patel et al. [26], emphasized the positive effect of the drug in spatial memory and motor learning preservation in treated models of brain hemorrhage. The major goal of our trial is to establish the role of glibenclamide as an adjunct treatment in the scenario of posthemorrhagic delayed neurological onset. T﻿he limitations of this study may be related to potential confounding factors, including baseline clinical conditions and methods of aneurysm treatment (clipping or coiling). However, randomization may automatically match the groups and prevent confounding.

### Trial status

This is protocol version 2.1, 1 May 2019. This trial began recruitment on 3 July 2018 and currently has a total of 36 recruited patients. Most of these patients are still in the follow-up period and will soon be interviewed by a psychologist. The recruitment/allocation is anticipated to be complete by 1 August 2019, and the final follow-up should last until 31 December 2019. This submission includes the SPIRIT checklist as Additional file 1.

## Data Availability

All data generated and/or analyzed during this study will be included in the published article and its supplementary information files. All generated data, tables and statistical analysis will be available to the public via scientific publication.
